### Sample size calculation

For Phase 1, we considered institutional delivery (a major outcome variable) as a basis for the sample size calculation. To estimate sample size, we took account of our longitudinal design that measures the same subjects before and after the intervention and assumed an intervention effect of 9% in improving institutional delivery beyond the current 48%
^
3
^. Assuming a p-value of 0.05, interclass correlation coefficient (ICC) of 0.009, a power of 80%, a total of 240 pregnant women from the intervention arm and another 240 pregnant women from the control arm are needed, for a total sample size of 480 pregnant women in each study phase. The assumptions of sample size also took into account feasibility and sample characteristics. The number of enumeration areas in the first phase was 80 per study arm, and approximately 5 women were expected to be eligible in each enumeration area. Based on the cross-sectional study design in Phase 2, we assumed 9% detectable difference between the study arms with an 80% power, which led to a sample of 531 for each study arm, taking account of 10% non-response rate. Approximately 106 enumeration areas will be reached from given the number of eligible women in each area. Both intervention and control arms will have an equal sample size in each phase, having 1:1 ratio of women between the intervention and control arms. As such, the total number of women to recruit across study arms in Phase 1 will be 1062.

For qualitative assessments, we use the same approach in Phase 1 and 2. An equal number of health workers (n= 32) are interviewed at mid-line (post-intervention of Phase 1) and end-line (post-intervention of Phase 2). The interviews with health workers explore the feasibility, acceptability, and scalability of the prototype solutions along with perceived program effects. The interviewees selected for Phase 2 may be the same service providers recruited from Phase 1 depending on their availability and engagement in the program. We have chosen 32 as the target sample size based on our best estimate about achieving data saturation. In each phase, we will also interview 20 pregnant women from the panel who recently delivered and were exposed to our HCD solutions. The qualitative interviews will be conducted only in the intervention sites.

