Nevertheless, this study will use a multi-level modeling framework to assess the intervention effect based on a difference-in-difference analysis by computing differences between baseline and midline within each arm, and then test this difference between intervention and control arms. A fixed effects model will first be used to observe this effect of the intervention. Kebele and PHCU will then be included as random intercepts to account for clustering within these levels. The estimated variance for random effects will show the amount of variability in the outcome that is explained by the clusters (i.e., how much of institutional delivery uptake is attributed to a kebele). If the coefficient of the interaction term is significant with the significant model fit, we will observe significant program effects. The identical analyses will be conducted with 4+ANC visits as the outcome variable. Other covariates will be included by comparing goodness-of-fit statistics (e.g., AIC, BIC) to improve the model fit. Proper model specification and diagnostic tests will be conducted to enhance the robustness of the results. Phase 2 data analysis will focus on comparing service utilization between intervention and control arms. Since we expect that study effectiveness will be stronger in Phase 2 with the implementation of enhanced solutions, we will also compare the study outcomes with baseline at Phase 1.

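### Phase 1's 240 women per arm cannot be reproduced from the stated inputs; under the planned difference-in-differences it gives 80% power only with an unstated within-woman correlation of about 0.75

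*Protocol article*

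**What the plan says.** The Sample size calculation section bases Phase 1 on institutional delivery. It "assumed an intervention effect of 9% in improving institutional delivery beyond the current 48" per cent, and gives the remaining inputs as "Assuming a p-value of 0.05, interclass correlation coefficient (ICC) of 0.009, a power of 80" per cent. It says of the design that "we took account of our longitudinal design that measures the same subjects before and after the intervention". From this it concludes that "a total of 240 pregnant women from the intervention arm and another 240 pregnant women from the control arm are needed". No within-woman correlation and no formula are given.

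The same section sizes Phase 2 as a cross-sectional comparison with the same 9% difference and 80% power, "which led to a sample of 531 for each study arm, taking account of 10% non-response rate". Allocation is equal in both phases, "having 1:1 ratio of women between the intervention and control arms".

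The Data analysis plan fixes the Phase 1 test as a difference-in-differences, "computing differences between baseline and midline within each arm, and then test this difference between intervention and control arms". Under Data collection and measurement, the outcome is the self-reported place of the most recent birth. Under Study design, 470 women were enrolled at baseline and 453 were interviewed at midline.

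**The concern.** Two calculations in one paragraph share the outcome, the effect and the power, yet Phase 1 needs half the women that Phase 2 needs before its non-response allowance. The reason offered is the repeated measurement of the same women. Repeated measurement does not by itself reduce the sample size of a difference-in-differences: the extra baseline variance has to be paid for, and at a correlation below about 0.5 the design needs more women than a post-only comparison. The within-woman correlation therefore decides whether 240 is enough, and it is the input that is not stated.

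The article relies on Phase 1. It cites a significant improvement in institutional delivery to justify a post-only Phase 2. If power was well below 80%, a significant estimate will tend to overstate the effect, and a null result on ANC visits, for which no power is claimed, would say little. The Discussions section also expects smaller effects in this constrained population than in other studies, which makes 9 points harder to detect.

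**Working it through.** **Inputs.** Proportions 0.48 and 0.57, 80% power, ICC 0.009 and 240 per arm come from Sample size calculation. About three women per enumeration area comes from Recruitment, and about five eligible women per area from Sample size calculation. Assumed here: two-sided 5%, 9% read as percentage points, and a control rate that stays at 48%. Then v0 = 0.48 × 0.52 = 0.2496, v1 = 0.57 × 0.43 = 0.2451, and (1.960 + 0.842)² = 7.849.

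**1. Phase 2 figure (reproduces).** Two proportions, pooled variance under the null: [1.960 × √(2 × 0.525 × 0.475) + 0.842 × √(0.2496 + 0.2451)]² / 0.09² = 482.1, so 483 per arm. 483 × 1.10 = 531.3, which matches the stated 531.

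**2. Phase 1 figure as a post-only comparison (does not reproduce).** Unpooled: 7.849 × 0.4947 / 0.0081 = 479, rounded up to 480. Pooled: 483. The design effect 1 + (m − 1) × 0.009 is 1.018 at m = 3 and 1.036 at m = 5, giving 492 and 501. Power at 240 per arm is about 51%, or 49 to 50% with the design effect. A one-sided test would still need 380.

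**3. Phase 1 figure as the planned difference-in-differences.** With within-woman correlation ρ, the variance per woman, summed over the arms, is

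V = [v0 + v1 − 2ρ√(v0·v1)] + 2·v0·(1 − ρ) ≈ 0.994 × (1 − ρ).

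Required n per arm = 7.849 × V / 0.0081 ≈ 963 × (1 − ρ). Setting this to 240 gives ρ = 1 − 240/963 = 0.75 (0.755 with the 1.018 design effect).

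Power at 240 per arm = Φ(0.09 / √(V/240) − 1.960), before clustering:

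| ρ | n per arm for 80% | Power at 240 |
|---|---|---|
| 0 | 963 | 29% |
| 0.3 | 674 | 39% |
| 0.5 | 482 | 51% |
| 0.6 | 385 | 60% |
| 0.7 | 289 | 72% |
| 0.75 | 241 | 80% |

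**4. How demanding 0.75 is.** Two binary variables with proportions 0.48 and 0.57, as in the intervention arm, cannot correlate above √[(0.48 × 0.43) / (0.57 × 0.52)] = √(0.2064 / 0.2964) = 0.83. At 0.75, the share of intervention women moving from a facility birth to a home birth would be 0.2064 − 0.75 × 0.2473 = 0.021, about 2%. The women are pregnant at baseline, so the baseline value can only be the place of an earlier birth. First-time mothers have none, and Table 1 does not exclude them. They contribute no pair, and the article does not give their number.

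**5. Women followed.** 453 / 2 = 226.5 per arm if split equally (the split is not given). At ρ = 0.75 power is 78% before clustering and about 76 to 77% with the design effect. For a post-only comparison at this size, the 80% detectable difference is about 13 points: with 0.48 and 0.61, 7.849 × (0.2496 + 0.2379) / 0.13² = 226.

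**The case against.** The strongest defence is that the two phases do not share all inputs. Phase 1 is a panel and Phase 2 a cross-section, so a smaller Phase 1 figure is not in itself a contradiction, and 531 cannot prove 240 wrong. That stands. So does the point that an article often leaves a formula or a within-subject correlation to the full protocol or analysis plan. The finding is therefore not that the correlation is missing. It is that an unconditional 80% is stated beside a list of inputs that does not deliver it.

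Unstated choices also move the figures. With a one-sided test, a correlation of about 0.68 suffices and power at 0.5 is 63%. A baseline-adjusted analysis would need about 0.71 and also has 63% at 0.5. But the Data analysis plan names difference-in-differences, and both alternatives still need a high correlation.

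A reader might infer that the design's true power is about 50% or lower. The documents do not support that: it holds for a post-only comparison, or for a correlation of about 0.5 or less, and no correlation is given. A reader might also infer that 240 came from a one-arm calculation that left out the control arm. Several routes give a figure near 240, including the planned analysis at 0.75, and the article does not say which was used.

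Finally, since a significant result for institutional delivery is already reported, the risk of misreading a null result on that outcome is moot. What remains is possible overestimation and the reading of the ANC results.

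**Conclusion.** The point holds in conditional form. No comparison between arms that uses only the printed inputs gives 240 per arm; a post-only comparison needs about twice that number. The planned difference-in-differences attains 80% at 240 only with a within-woman correlation of about 0.75, against a ceiling of about 0.83 for proportions of 48% and 57%. Power falls to about half at 0.5 and to under a third at 0. After the observed loss to follow-up, 0.75 no longer quite reaches 80%, and women without an earlier birth would lower power further. The failure to reproduce is certain given two-sided testing and an absolute 9-point effect. The power actually achieved is not known until the correlation and the number of complete pairs are reported.

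**What to change.** In Sample size calculation, replace the unconditional 80% statement for Phase 1 with the power, or the 80%-power detectable difference, of the planned difference-in-differences across a stated range of within-woman correlation. State the formula and the sidedness. Include the correlation observed in the Phase 1 panel and the number of women with both a baseline and a midline value. For reference, add that a post-only comparison has about 50% power for 9 points, or 80% power for about 13 points at about 226 per arm. Do not print about 50% as the design's definite power.

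In the Phase 1 report, interpret institutional delivery and ANC by effect estimates with confidence intervals, and do not read a non-significant ANC result as evidence of no effect.

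The cost is one revised paragraph and a short calculation on data already collected. No new participants are needed, but the stated power will probably look less favourable.

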### Recruitment

After obtaining a list of all interested women from health extension workers and health development armies, data collectors visit the women in person to screen their pregnancy status and vulnerability level to assess their eligibility. With the woman’s verbal consent, the data collector administers the pregnancy screening tool to identify her pregnancy status. Only women at 5+ months of pregnancy and aged 15–49 are considered eligible. If eligible, she is screened for her vulnerability level, assessed through the vulnerability screening tool. Those considered to be moderately to highly vulnerable are eligible and entered into the sampling frame. Women who score at least 9 out of the maximum 20 vulnerability screening questions will be identified as a study participant. All responses to the screening questions will be entered into the data collectors’ mobile phone application that automatically determines pregnant women’s eligibility during the visit. 

All eligible women are entered into our sampling frame. After listing eligible pregnant women, we aim to recruit approximately three women per enumeration area to achieve our target sample size. If an enumeration area has five or fewer eligible women, they are all contacted for recruitment. If there are more pregnant women than the minimum required number of pregnant women, we randomly select the required number. If a woman is not interested or available for participation, we contact the next randomly selected woman for recruitment. Recruitment continues until our sample size is reached, expanding to other enumeration areas if necessary. Recruitment in Phase 1 was completed in this way, and Phase 2 recruitment will follow this procedure.

For the qualitative assessment, recently delivered women who receive our intervention and health workers in the intervention sites are purposively recruited. Purposive selection of the sample allows us to understand the experiences of engaging in our implementation process among diverse individuals. For women, the selection criteria include: 1) residing in Siraro and Shalla woredas, 2) being exposed to the HCD solutions during their last pregnancy, and 3) having delivered after receiving the solutions. To further obtain diverse and in-depth experiences among our sample, we prioritize recruiting women who are in earlier gestational ages (5

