### Data analysis plan

**
*Quantitative data analysis*.** First, we will conduct a series of bivariate tests, including chi-square and t-tests, across treatment and control arms based on baseline and endline data. The purpose of conducting bivariate tests is to identify differences between the study arms for each potential confounding factors, given the possibility of quasi-experimental design not ensuring baseline matching between intervention and control arms. If any differences are observed, they will be controlled for in subsequent regression analyses. We will also identify types of missing data to determine whether missingness occurs in a systematic manner, which will help us determine the appropriate remedial measure to adopt.

Since this project will conduct various implementation activities at the PHCU level, the analysis will take account of clustering at the level. Further, because
*kebeles* (akin to villages) are clustered within PHCUs, we will also consider clustering at the
*kebele* level. Given the nested nature of this study, multi-level modeling is considered appropriate because it provides both cluster-specific and population-averaged estimates simultaneously by defining both random effects and fixed effects, respectively. Prior studies that represented similar scenarios, however, have shown that estimated coefficients and standard errors are usually not biased, even with a sample size as low as 5 to 10 at Level 1
^
27,
28
^, and with many independent variables and interaction terms
^
29
^.

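### The sample size section gives Phase 2 two incompatible totals, an enumeration-area count that does not fit the recruitment rule, and a figure of 531 per arm that appears to carry no design effect

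*Protocol article*

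**What the plan says.** All the sizes stand in one paragraph of the protocol article, under Sample size calculation.

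- **Phase 1.** The basis is institutional delivery at 48%, a 9% improvement, 80% power, a p-value of 0.05 and an "interclass correlation coefficient (ICC) of 0.009". This gives 240 per arm, "for a total sample size of 480 pregnant women in each study phase". There were 80 enumeration areas per arm, with about five eligible women expected in each.
- **Phase 2.** A cross-sectional comparison with a 9% difference and 80% power, "which led to a sample of 531 for each study arm, taking account of 10% non-response rate". No ICC, design effect or control rate is named for this calculation. "Approximately 106 enumeration areas will be reached"; whether that is per arm or overall is not said.
- **Closing total.** "the total number of women to recruit across study arms in Phase 1 will be 1062".

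Elsewhere, Study design reports 470 women enrolled in Phase 1. Recruitment states that "we aim to recruit approximately three women per enumeration area to achieve our target sample size", that a woman who declines or is unavailable is replaced by the next one randomly selected, that recruitment expands to further areas until the target is reached, and that Phase 2 uses the same procedure. The Data analysis plan says that clustering by PHCU will be taken into account and, for kebeles within PHCUs, that "we will also consider clustering at the" kebele level.

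**The concern.** Phase 2 has not been recruited, so these numbers are still instructions for fieldwork. As written, the Phase 2 total is either 480 or 1062, and the number of areas to visit depends on whether three or five women are taken in each. A team cannot follow both members of either pair.

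The second issue is what 531 allows for. Phase 1 was sized with an ICC and the analysis is to account for clustering, yet the Phase 2 figure looks like one for independent women. If so, the stated 80% power does not describe the analysis that is planned.

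**Working it through.** **Inputs.** From Sample size calculation: 48% control rate (given for Phase 1 and carried to Phase 2 here as an assumption), 9-point difference, alpha 0.05 (two-sided assumed), 80% power, 10% non-response, ICC 0.009, five eligible women per area, 106 areas. From Recruitment: about three women per area.

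**1. Totals.** 2 x 240 = 480 and 2 x 531 = 1062. So 1062 is the Phase 2 total, although it is labelled Phase 1. It contradicts 480 as the size of each phase, and Phase 1 enrolled 470.

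**2. Enumeration areas.**
- Phase 1: 80 x 3 = 240 per arm, which is consistent.
- Phase 2 at five per area: 106 x 5 = 530, so 106 fits 531 if it is a per-arm count.
- Phase 2 at three per area: 531 / 3 = 177 areas per arm; 106 x 3 = 318.

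**3. Reproducing 531.** Pooled two-proportion formula, mean rate 0.525:

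n = [1.960 x sqrt(2 x 0.525 x 0.475) + 0.842 x sqrt(0.48 x 0.52 + 0.57 x 0.43)]^2 / 0.09^2 = 482.1 per arm.

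482.1 x 1.10 = 530.3, rounded up to 531. The match is exact with no design effect. Dividing by 0.90 instead gives 535.7, so 536, about five more women per arm.

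**4. Adding the Phase 1 ICC.** Design effect DE = 1 + (m - 1) x 0.009, required size = 482.1 x DE / 0.90, and power evaluated at (number analysed) / DE. If 10% are lost, 531 x 0.90 = 478 are analysed.

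| Women per area, m | DE | Required per arm | Power, 478 analysed | Power, 531 analysed |
|---|---|---|---|---|
| 1 (no clustering) | 1.000 | 536 | 79.7% | 83.7% |
| 3 | 1.018 | 546 | 79.0% | 83.0% |
| 5 | 1.036 | 555 | 78.2% | 82.4% |

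**5. If the ICC applies at kebele or PHCU level.** The protocol gives no cluster counts. The range of K = 8 to 40 clusters per arm is assumed, with m = (number analysed) / K and the ICC held at 0.009.

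| K per arm | DE, 478 analysed | Power | DE, 531 analysed | Power |
|---|---|---|---|---|
| 8 | 1.53 | 62% | 1.59 | 64% |
| 20 | 1.21 | 72% | 1.23 | 76% |
| 40 | 1.10 | 76% | 1.11 | 79.7% |

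**The case against.** Several counter-arguments have force.

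- **The power loss may be small or absent.** With the protocol's own ICC at enumeration-area level the shortfall is one to two points. Under the replacement rule 531 may actually be analysed, and power then exceeds 80% with the design effect included. This stands, although replacement does not cover women lost after recruitment, and the protocol does not say which kind of loss the 10% represents.
- **The missing design effect is an inference.** Other control rates also give 531 with clustering included: 37% versus 46% needs 469.3, and 469.3 x 1.018 / 0.90 = 530.8. This stands as a caveat. However, 48% is the only rate the protocol states, and it matches exactly without a clustering term.
- **The inflation method hardly matters.** Multiplying by 1.10 rather than dividing by 0.90 is worth about five women per arm and is itself inferred. It is not pressed here.
- **Recruitment would not stop short.** A reader might infer from 106 areas at three women each that Phase 2 would end at 318 per arm, 40% below target. The documents do not support that: recruitment continues into further areas until the target is met. All eligible women are also contacted where an area has five or fewer, so five per area is possible. What remains is a conflict between the stated take and the planned number of areas.
- **The lower power figures rest on assumed cluster counts.** They do. The protocol also does not say at which level the ICC of 0.009 applies, and its random-intercept model is described for the baseline-to-midline comparison. The general statement on PHCU and kebele clustering is not limited to Phase 1, so the question remains open for Phase 2.

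**Conclusion.** The contradictions in the totals and in the area count are certain and need no outside assumption: 480 for each phase against 531 per arm, 1062 attached to the wrong phase, and 106 areas against a take of three.

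The point about 531 holds in a limited form. It most plausibly omits clustering, given the exact match at 48% versus 57%. Applying ICC 0.009 at three to five women per area raises the requirement by 15 to 24 per arm (546 - 531 and 555 - 531). A reader might conclude that Phase 2 is clearly underpowered; the documents do not show that. At enumeration-area level, power lies between about 78% and 83%, depending on whether losses are replaced. It would be materially lower, about 62-76% with 478 analysed or 64-80% with 531, only if the same ICC applies to kebeles or PHCUs numbering 8 to 40 per arm, which is an assumed range.

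**What to change.** 1. State the total as 480 for Phase 1 and 1062 for Phase 2, and remove the statement that each phase has 480.
2. State one take per enumeration area for Phase 2, with the matching number of areas per arm: 106 at five women or 177 at three. Bring Recruitment into line and say that the count is per arm.
3. Give the Phase 2 control rate, and say whether the 10% covers refusals, which are replaced, or women lost after recruitment.
4. Restate Phase 2 power for 531 per arm, or the difference detectable with 80% power, using a design effect at the level of clustering to be analysed and the actual numbers of kebeles and PHCUs. The ICC and control rate can now be estimated from Phase 1.

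The cost is a text correction and one recalculation. No additional women are needed. At three per area more areas would have to be planned, and the stated power may come out somewhat below 80%.
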